| 2.1.3 Background       | 
1. Information in informed consent forms
 
 
- Since the declaration of Helsinki has presented the ethical principles for clinical trials that potential participants should be provided with adequate information regarding study such as study objectives and procedure, most clinical studies are conducted in accordance with the declaration.
 
- Current medical studies are also conducted in accordance with the four principles of medical ethics (autonomy, non-maleficence, beneficence, and justice). (Gillon, 2003; Harris, 2003).
 
- Sufficient information in participant information leaflets or informed consent forms provided to potential participants facilitates informed consent which is assumed to serve principles of medical ethics, especially autonomy.
 
- An informed consent document is one of the most common ways to provide key information of clinical trials to potential participants. In key information is included study objectives, procedures, possible harms and benefits, and alternatives to participation.
 
 
2. Placebo information in informed consent forms of randomized clinical trials
 
 
- A recent study revealed that informed consent documents of qualified randomized clinical trials provide ample information on the benefits of the test intervention while the information on placebo control was lacking or inaccurate and there is a room for improvement in the current standard of informed consent documents (Bishop, 2012)
 
- Another study also presented that some of informed consent documents of acupuncture randomized clinical trials partially provided placebo information or omitted placebo information and this can affect blinding of participants and directions of trial outcomes (Cheon, 2018).
 
 
3. Previous randomized clinical trials that manipulated placebo information at the beginning of the study and debriefed true placebo information or true study hypothesis at the end of study.
 
 
- A recent randomized clinical trial investigated whether perception of migraineurs toward assigned intervention, i.e., a real drug or placebo, influenced the effect size of drug or placebo with hiding true study objectives at the beginning and debriefing true hypothesis. This study design facilitates (Kam-Hansen, 2014).
 
- Another randomized clinical trial provided participants with placebo and informed it is a drug that is frequently used. This study aimed to investigate the impact of framing of side effect on adverse event reporting randomized participants into differently, i. e., positively or negatively. At the end of the study, participants were debriefed to the
 
 |

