|  | 
 
3. Induction of delayed onset muscle soreness model
 
 
- Measurement of 1RM in the non-dominant arm
 
- Repetitive arm-curl exercise in the non-dominant arm using 1RM weighted dumbbell
 
- Measurement of muscle discomfort in the non-dominant arm with VAS
 
- Measurement of PPT in the non-dominant arm
 
 
4. Acupuncture treatment
 
 
- RA (PC2, LI4, LI11 and LU5 of the non-dominant arm) and PA (two points on the muscle belly of biceps brachii, 1 cun proximally from LI11, and 1 cun laterally from PC2 of the non-dominant arm) will be performed for 15 minutes once daily for three consecutive days with manipulation (by rotating 180 degrees clockwise and counter-clockwise in a frequency of 2 Hz at immediately, 3, 6, 9, and 12 minutes after needle insertion)
 
 
5. After acupuncture treatment
 
 
- To fill out de-qi questionnaire
 
- Measurement of muscle discomfort in the non-dominant arm with VAS
 
- Measurement of PPT in the non-dominant arm
 
 
 <hr/> 
 
1. Before acupuncture treatment
 
 
- Adverse event monitoring
 
- Measurement of muscle discomfort in the non-dominant arm with VAS
 
- Measurement of PPT in the non-dominant arm
 
 
2. Acupuncture treatment
 
 
- RA (PC2, LI4, LI11 and LU5 of the non-dominant arm) and PA (two points on the muscle belly of biceps brachii, 1 cun proximally from LI11, and 1 cun laterally from PC2 of the non-dominant arm) will be performed for 15 minutes once daily for three consecutive days with manipulation (by rotating 180 degrees clockwise and counter-clockwise in a frequency of 2 Hz at immediately, 3, 6, 9, and 12 minutes after needle insertion)
 
 
3. After acupuncture treatment
 
 
- To fill out de-qi questionnaire
 
- Measurement of muscle discomfort in the non-dominant arm with VAS
 
- Measurement of PPT in the non-dominant arm
 
 
 <hr/> 
 
1. Before acupuncture treatment
 
 
- Adverse event monitoring
 
- Measurement of muscle discomfort in the non-dominant arm with VAS
 
- Measurement of PPT in the non-dominant arm
 
 
2. Acupuncture treatment
 
 
- RA (PC2, LI4, LI11 and LU5 of the non-dominant arm) and PA (two points on the muscle belly of biceps brachii, 1 cun proximally from LI11, and 1 cun laterally from PC2 of the non-dominant arm) will be performed for 15 minutes once daily
 
 
 |

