| 2.3.9 Statistical plan | 
Main outcomes are pain outcomes and blinding of participants
 
 
- Pain outcomes: PPT and VAS.
 
✓ Two way ANOVA is considered as the way of statistical plan as it can analyze effect of two interventions (acupuncture and informed consent)
 
✓ The effect will be assessed as statistically significant when p value is under 0.05.
 
- Blinding of participants will be analyzed using a Blinding Index (BI, Bang, 2004).
 
- Scores of Myers credibility index, ABS, STAI-X, acupuncture credibility test, and de-qi questionnaire will be analyzed using two-way ANOVA with independent variables (type of acupuncture and placebo information disclosure). A p value less than 0.05 will be considered as statistically significant.
 
- Adverse events will be reported with details and causal relationship with acupuncture will be also assessed. Whether frequency of adverse events that has causal relationship with acupuncture differ between acupuncture types will be analyzed using chi-squared test or Fisher's exact test. A p value less than 0.05 will be considered as statistically significant.
 
- Demographic data will reported descriptively, i.e., continuous variables will be described with mean <math>\pm</math> standard deviation and categorical variables will be shown as frequency (%).
 
                                                                                                                                                                                 |

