| 2.3.10 Safety securing | 
 
- Monitoring adverse events
 
- Interviewing with participants at day 2 and day 3 visit
 
- Any adverse event will be described with details and numbers of adverse events have causal relationship or do not have one will be also described.
 
- Adverse events that are frequently reported following acupuncture: bruising, local pain, and minor bleeding (MacPherson, 2001)
 
- Adverse events refer to undesired and unintended signs (e.g., abnormalities in laboratory tests), symptoms, or diseases occurring after the treatment in the study. The events do not necessarily have a causal relationship with the treatment.
 
- Assessment of the severity (following Common Terminology Criteria for Adverse Events, CTCAE) 
 
✓ Grade 1 Mild; asymptomatic or mild symptoms; clinical or diagnostic observations only; intervention not indicated.
 
✓ Grade 2 Moderate; minimal, local or noninvasive intervention indicated; limiting age appropriate instrumental ADL*.
 
✓ Grade 3 Severe or medically significant but not immediately life-threatening; hospitalization or prolongation of hospitalization indicated; disabling; limiting self care ADL**.
 
✓ Grade 4 Life-threatening consequences; urgent intervention indicated.
 
✓ Grade 5 Death related to adverse event.
 
 
 
- Assessment of the causality (following WHO-UMC Causality Categories) 
 
✓ Certain
 
 
 
 |

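### The only adverse-event test is limited to events judged related and to needle type, leaves out the consent form, and no scheduled inquiry follows the third session

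*Protocol*

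**What the plan says.** **The test.** Section 2.3.9 asks whether "frequency of adverse events that has causal relationship with acupuncture differ between acupuncture types". This "will be analyzed using chi-squared test or Fisher's exact test", and "A p value less than 0.05 will be considered as statistically significant". It is the only hypothesis test for adverse events in the protocol.

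**The other outcomes.** The same section analyses the questionnaire scores by two-way ANOVA with "independent variables (type of acupuncture and placebo information disclosure" as factors. It plans two-way ANOVA for the pain outcomes as well, to cover both interventions.

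**The listing.** Sections 2.2.9 and 2.3.10 define adverse events regardless of causality. Section 2.3.10 has every event described, and "numbers of adverse events have causal relationship or do not have one will be also described".

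**The causality judgement.** Section 2.2.9 gives it to the investigator, using the WHO-UMC categories. Section 2.3.5 says the practitioner cannot be blinded and claims blinded assessment for PPT and VAS. It says nothing about masking the person who judges causality.

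**The timing.** Section 2.3.10 lists "Interviewing with participants at day 2 and day 3 visit". In 2.3.4 the item "Adverse event monitoring" stands under the pre-treatment heading on those two visits. After the third session the schedule lists de-qi, VAS, PPT, acupuncture credibility and blinding, and then debriefing. Section 2.2.9 also collects events through symptom reports and through the investigator's observation and monitoring.

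**The concern.** Relatedness is judged after randomisation and can itself depend on the needle. The placebo needle has an insertion depth of 0 mm (2.3.6), and all needling is in the arm made sore by exercise. Section 2.3.10 names local pain as a frequent event after acupuncture. Local pain could be put down to the needle in one group and to the exercise in the other. If so, a test confined to related events partly compares attribution rather than harm.

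The stated objective (2.1.2) is the effect of placebo information on study results and blinding. Section 2.1.3 cites as a precedent a trial of which it says: "This study aimed to investigate the impact of framing of side effect on adverse event reporting". Adverse events are the one tested outcome in 2.3.9 for which the disclosure factor is dropped.

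The third session is followed by debriefing, which reveals the needle type and the consent form. A report made after that comes from an unblinded participant, so the useful moment for a structured question is before it.

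**Working it through.** **Stated figure.** The protocol gives no adverse-event rate, power or sample size, so there is no adverse-event figure to reproduce. The overall sample size in 2.2.4 does reproduce: 80 / (1 − 0.10) = 88.9, rounded up to 89.

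**Effect of the relatedness restriction (illustration).**
- From the protocol: target of 80 participants, two needle types, Fisher's exact test, significance level 0.05.
- Assumed: equal allocation, so 80 / 2 = 40 per needle type; a two-sided test; one yes/no outcome per participant; the true event risk p, equal in both needle types; the shares of events judged related, r for real and s for placebo needles.
- Formula: the tested risks are p × r and p × s. The exact rejection probability is the sum of Bin(i; 40, p × r) × Bin(j; 40, p × s) over all tables (i, j) with Fisher p < 0.05.

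| True risk p, both groups | Any-cause test | Related only, 80% / 80% | Related only, 80% / 50% | Related only, 90% / 30% |
|---|---|---|---|---|
| 20% | 2.8% | 2.6% | 7.0% (16% vs 10%) | 25.9% (18% vs 6%) |
| 30% | 2.8% | 2.9% | 11.8% (24% vs 15%) | 47.1% (27% vs 9%) |
| 40% | 3.0% | 2.8% | 16.6% (32% vs 20%) | 64.9% (36% vs 12%) |

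The brackets give p × r against p × s; for example, 0.30 × 0.80 = 0.24 and 0.30 × 0.50 = 0.15. The restriction does no harm when attribution is equal. It inflates false positives only when attribution differs.

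**Coverage of the sessions.** A scheduled inquiry follows sessions 1 and 2 but not session 3, so it covers 2 of 3 sessions. With an assumed independent event risk q per session, the chance of at least one event is 1 − (1 − q)³ over three sessions and 1 − (1 − q)² over the two that are followed up:
- q = 5%: 14.3% against 9.8%
- q = 10%: 27.1% against 19.0%
- q = 20%: 48.8% against 36.0%

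The gap is the most that scheduled inquiry alone could miss. Symptom reports and observation would recover an unknown part of it.

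**Power.** With 40 per group, Fisher's exact test has about 53% power for an assumed 30% against 10%. An interval estimate will therefore say more than a p value.

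**The case against.** Several stronger readings are tempting, and the protocol does not support them.

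- **That unrelated harms are not counted.** Section 2.3.10 has every event described and counts related and unrelated events. Only the significance test is restricted.
- **That an unblinded person judges causality.** The practitioner is unblinded, but 2.2.9 gives the judgement to the investigator and leaves that person's masking unstated. Distortion is a conditional risk, and the attribution shares above are assumptions.
- **That events after the third session will be missed.** Symptom reports and investigator observation remain, participants stay for further measurements and a debriefing interview, and the Day 3 interview in 2.3.10 is not itself tied to a time before needling. Only the schedule places it there.
- **That the test wrongly counts events instead of participants.** The wording is ambiguous and fits a table of participants with an event. The counting unit is commonly settled in a statistical analysis plan.

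It can also be said that the precedent in 2.1.3 varied the framing of side effects, whereas here the consent wording varies only the description of the control needle, and that the main outcomes are pain and blinding. Both are true and lower the weight of the point. They do not explain why 2.3.9 tests adverse events at all and yet leaves out the factor that the trial exists to study.

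**Conclusion.** The point holds in a limited form. The protocol fixes one adverse-event test, restricts it to a judgement not stated to be masked, and omits the consent form that it uses for pain and all questionnaire scores. It schedules no inquiry after the third of three sessions.

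The size of any distortion cannot be derived from the protocol. Under the assumptions above, the false-positive rate is about 3% with equal attribution, 7% to 17% with a moderate imbalance and 26% to 65% with a large one. Severity is minor to moderate: adverse events are not a main outcome, 2.2.4 calls the study exploratory, and all events are listed in any case.

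**What to change.** **Section 2.3.9.** Compare the number of participants with at least one adverse event of any causality, once by needle type and once by consent form. Give the risk difference with its 95% confidence interval and Fisher's exact test. Show related events as a descriptive summary.

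**Section 2.3.4.** Add one adverse-event question after the third session and before debriefing. If participants are contacted after debriefing, report those events descriptively for safety only and keep them out of the comparisons, because participants are then unblinded.

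**Cost.** Some wording and one question on Day 3; the comparison by consent form uses groups and data that the trial already has. The downside is that soreness is induced in every participant. Counted as an event, it may become common in all groups and dilute differences, so it should be tabulated separately.
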